## Abstract

**Introduction:**

Postpartum depression (PPD) is widely and profoundly affecting family and social stability. But now the consultation rate of overall PPD population is still not ideal for practical reasons. This study observes the effectiveness of Internet-based peer education, a promising treatment approach that may effectively and fairly serve the PPD group, so as to benefit more people in the future.

**Objectives:**

This study integrates internet-based peer education to serve PPD groups effectively and equitably, aiming to benefit more people. It explores IPE’s efficacy vs. RHE in reducing symptom severity at 6-week intervention and 16-week follow-up.

**Methods:**

This study is a randomized, parallel, and controlled trial, consist of a 6-week treatment period along with a 12-week follow-up period. Eighty-eight patients diagnosed as PPD will be recruited. They will be randomly assigned to one of two groups, internet-based peer education (IPE) group and regular health education (RHE) group, in a 1:1 ratio. Both groups will receive RHE along the 6-week treatment, while subjects in IPE group will receive 6-week online peer education additionally. The primary outcome is the response rate based on scores of 17-item Hamilton Depression Rating Scale at the week 6 and 12. The secondary outcomes include Edinburgh Postpartum Depression Scale (EPDS), World Health Organization Quality of Life Scale Brief (WHOQOL-BREF) and Self-Efficacy to Manage Chronic Disease Scale (SEMCD). All these scales will be evaluated at baseline, 1, 2, 4, 6, and 12 weeks after the initiation of intervention.

**Conclusion:**

The results of this RCT on Internet-based peer education for postpartum depression will provide an assessment of the feasibility of the protocol and data for power calculations to inform the development of a larger scale trial.

## Introduction

1

As known, pregnancy is a complicated and vulnerable period for women, and it comes with a lot of unexpected difficulties (1). Postpartum depression (PPD) is one of the most common complications in perinatal period (2), classified as a subtype of major depressive disorder (MDD) with postpartum onset in American Psychiatric Association’s Diagnostic and Statistical Manual of Mental Disorders, fourth edition (DSM-IV) (3).

In high-income countries, the prevalence of postpartum depression (PPD) ranges from 6.9 to 12.9%, while in low- and middle-income countries, it exceeds 20% (4). This global variability underscores PPD as a pressing worldwide mental health concern, with far-reaching impacts on maternal health, child development, and family functioning (5, 6). Notably, prenatal depression has been identified as a key risk factor that significantly elevates the likelihood of PPD (7). Moreover, beyond its immediate effects on maternal wellbeing, PPD exhibits a striking comorbidity with depression in children and adolescents (8), further extending its public health relevance across the lifespan.

No matter in China or worldwide, women in postpartum period are increasingly vulnerable to suffer from poor mental health because of raising stress and less accessible social support (9). According to a population-based survey, after implementation of China’s universal two-child policy, it is pretty common that poor mental health outcomes still exist among women giving birth a second time (10). Unfortunately, due to a variety of reasons, such as lack of knowledge (11), perceived stigma (12), and health care system barriers (13), mothers with PPD prefer not to seek professional help.

What is inspiring, peer education services greatly benefit for recovery of people with mental health problems (6). Peer education is a structured intervention where individuals with lived experience of a specific condition (or similar life circumstances) provide support, share practical skills, and facilitate empowerment among those currently facing similar challenges (14). Peer educators can act as positive role for whom are currently experiencing mental distress by sharing real and useful skills they have acquired during their own experiences (9). It has to be notified that peer educators could not provide mental counsel but the information about depression, treatments, self-management and motivation for them to seek for needed professional services (10). But in other hand, peer educators may be more effective than mental health professionals at reducing stigma, enhancing attitudes toward mental health therapy because they share demographics with consumers (e.g., gender, age, income, etc.) and have personally experience involving mental illness (11). Moreover, peer education can help vulnerable groups that require mental health care but may feel excluded from the mainstream mental health system (12).

In this Internet age, a huge number of people can be offered low-threshold therapies online, regardless of time or location (15). A study shows that psychiatric patients use the Internet as frequently as the general population for engaging in online programs and accessing online health-related information (16). In addition, human support has repeatedly been shown to have a positive effect on effectiveness of and adherence to Internet-based interventions (17, 18). It has been shown in mental disorders that support provided by clinicians or coaches via telephone, email, and chat rooms could enhance adherence (19, 20). Consequently, online supportive program might be a promising approach to improve the accessibility, fairness, completeness, and quality of treatment for PPD population.

In the contemporary digital age, the relationship between peer education and internet—based interventions is intricate and mutually beneficial. Internet—based interventions offer a novel and far—reaching platform for the implementation and expansion of peer education.

Through online forums, instant messaging, and pre—recorded videos, they can disseminate information, share their personal experiences, and provide continuous motivation to those in need, regardless of physical location.

So the integration of internet services into mental health care has shown notable developments, particularly in leveraging digital platforms to address various psychological issues. Studies have explored the impact of internet use on mental health, with research on older adults indicating that internet engagement can influence psychological wellbeing through mechanisms like social equity perception (21), while also highlighting evolving research trends in this domain (22).

In healthcare services, internet-based peer education has emerged as a promising intervention. For instance, continuous peer education via online platforms has been applied to improve negative emotions, sleep quality, and self-care abilities among abortion patient (23). Similarly, “internet +” peer education models have effectively enhanced self-management behaviors and disease control in type 2 diabetes patients (24). These cases demonstrate the potential of digital peer support in complementing traditional healthcare.

However, a significant knowledge gap exists regarding the application of internet-based peer education in treating postpartum depression. While existing literature covers other populations and health issues, there is a lack of in-depth research on how such digital peer interventions can be tailored to address postpartum depression specifically within the Chinese context, leaving a critical area unexplored for optimizing mental health support in this vulnerable group.

This study aims to combine peer education with Internet-based intervention, maximize the advantages of two treatments, and explore a treatment approach that can effectively and fairly serve the PPD group, so as to benefit a wider range of population in the future.

The primary objective of the study is to investigate the efficacy of the Internet-based Peer Education (IPE) regarding changes in symptom severity compared to control group using Regular Health Education (RHE) during a 6 weeks intervention period and at the follow-up assessments at 12 weeks. Referring to previous evidence, we hypothesize that the IPE group will be superior compared to RHE group in reducing depressive symptoms directly after the 6 weeks of intervention, and at follow-up.

The secondary objective is to examine health related quality of life, the self-management ability and safety. We hypothesize, that the IPE group will lead to a significantly greater quality of life, better self-management and less adverse event than RHE group.

## Methods

2

### Study design

2.1

This is a two-arm randomized controlled clinical trial (RCT) of parallel design comparing the effect and safety of a guided Internet-based peer education (IPE) with regular health education (RHE) after the 6-week intervention and at 12-week follow-up (Figure 1). All participants will receive RHE. Participants of the intervention group will additionally receive the IPE. Those evaluated tools containing 17-item Hamilton Depression Rating Scale (HDRS17), Edinburgh Postnatal Depression Scale (EPDS) (25), WHOQOL, Self-Efficacy for Managing Chronic Disease Scale (SMCDS).

**Figure 1 fig1:**
[figure not shown]
Trial flow.

This clinical trial is conducted and reported in accordance with the CONSORT-supplement for pragmatic RCTs, and is carried out in Shenzhen Traditional Chinese Medicine Hospital, a tertiary hospital, in July, 2023 to March, 2025. The trial has been approved by the institutional review board of the Shenzhen Traditional Chinese Medicine Hospital Ethics Committee (No. K2023-029-01). This study has been registered on June 19, 2023, with the Chinese Clinical Trial Registry, identification number ChiCTR2300072601.

Recruitment has begun at July, 2023 and will continue until the target sample size has been reached before March 2025. Different recruitment channels will be used: The study will be promoted primarily by WeChat Official Account of Shenzhen Traditional Chinese Medicine Hospital to all subscribers. And persons with interests will finish an online-pre-screening questionnaire then those who meet the criteria will be contacted for further investigation. Besides, participants will be recruited from the Postpartum Pelvic Floor Rehabilitation Clinic. After primary screening with EPDS, those score over 12 will be given the leaflets of this subject by their attending doctors. With this recruitment strategy, we will recruit a sample consisting of patients searching either online help or seeking help from clinic.

### Inclusion and exclusion criteria

2.2

#### Inclusion criteria

2.2.1

Patients who provide written consent will be included in the study if they meet the following criteria: (1) age 20–49; (2) meet the Diagnostic and Statistical Manual of Mental Disorders (DSM-IV) criteria for postpartum depression, diagnosed as PPD by a psychiatrist; (3) score of EPDS >12 points, score of HDRS17 > 7, ≤24; (4) volunteer to participate in this study, and can complete the scale evaluation; (5) the onset occurs within 12 months after childbirth.

#### Exclusion criteria

2.2.2

Patients will be excluded who meet criteria for (1) bipolar disorder (according to DSM-IV diagnostic criteria), severe mental disorders such as schizophrenia; (2) with intellectual disability or difficulty in understanding the content of the questionnaire due to brain disease or other reasons, or unable to effectively talk; (3) pregnancy; (4) HDRS-17 suicidality item score >2; (5) suicidal behavior in the past year.

### Consent procedure

2.3

Whose EPDS score over 12 will be introduced to a psychiatrist for further diagnosis of PPD. After diagnosis, researchers will preliminarily introduce this program through the mobile phone, then invite the volunteer for a face-to-face interview. All interviews will be launched in a quiet and dedicated room.

First, the researcher explained the program in detail to the interviewee in a one-to-one setting and determined if the interviewee met all the inclusion criteria and did not meet the exclusion criteria. If all conditions were met, the researcher would use the 17-item Hamilton Depression Rating Scale (HDRS17) to assess depressive symptoms and ask the interviewee whether she would be willing to participate. After clear understanding the benefits and potential risks of this research, those who are willing to participate in will sign written informed consent. Participants will be not compensated for study participation.

### Randomization and allocation

2.4

The randomization was conducted using a computer-generated random number table (produced by SPSS 26.0 software) to ensure the unpredictability of group assignments. A total of 88 random numbers were generated, and each number was correspondingly assigned to either the intervention group (Internet-based peer education group) or the control group in a 1:1 ratio, with 44 subjects allocated to each group.

For allocation concealment, the research assistant who was not involved in subject recruitment prepared sequentially numbered opaque brown paper envelopes. Each envelope contained a card indicating the subject number, the generated random number, and the corresponding group assignment. These envelopes were sealed and stored in a locked cabinet to prevent premature disclosure.

When a qualified subject was enrolled, the researcher opened the envelopes in strict sequence according to the enrollment order (i.e., the first enrolled subject received the first envelope, the second subject the second envelope, and so on). The subject was then allocated to the group specified in the opened envelope. This procedure ensured that neither the researchers nor the subjects could predict the group assignment before enrollment, thus minimizing selection bias.

### Blinding

2.5

This study obeys the principle of blinding, and the separation of researchers, therapists and statisticians will be strictly implemented throughout the study. The efficacy evaluation during the observation is conducted by dedicated raters (research doctors, nurses, or postgraduates) who are unaware of the grouping status. For statistician blinding, the statisticians involved in data analysis are also kept blind to the grouping information. In case of emergency, the researcher could inform the doctor of the subject’s condition, so that the appropriate treatment could be taken. An emergency envelope with the subject’s random number and treatment plan will be prepared in advance, so that the doctor could open it in necessary.

### Interventions

2.6

#### Internet-based peer education

2.6.1

On the basis of RHE, Internet-based peer education will be used for therapeutic intervention. Participants in treatment group will receive RHE and IPE. The specific methods of IPE are as follows:

##### Intervention materials

2.6.1.1

(1) Digital platforms: WeChat (a widely used social communication application), utilized for creating dedicated education groups and facilitating real-time interactions.(2) Educational content: Articles and videos covering postpartum health (diet, exercise, neonatal feeding skills), mental health knowledge, emotional management techniques, and peer self-management experiences.(3) Training materials: Curricula for peer educator training, including modules on postpartum health, mental health, and emotional management, developed by the steering group.

##### Procedures

2.6.1.2

(1) Steering group establishment: A multidisciplinary team is formed to oversee intervention design, peer educator training, and quality assurance.(2) Peer educator selection and training: Eligible PPD patients are recruited, trained over 2 weeks, and assessed for competence before participation.(3) Group formation: Enrolled subjects are assigned to WeChat education groups (maximum 11 subjects per group) containing steering group members, peer educators, and participants.(4) Intervention implementation: Under the leadership of the guidance team, peer educators are trained and supervised to implement interventions for the subjects. The intervention measures include:i. The guidance team disseminates curated postpartum dietary, exercise, and psychological adjustment content every Monday, Wednesday, and Friday, with a monthly communication plan;ii. Peer educators provide weekly updates on member dynamics and needs every Friday, with the guidance team responding and adjusting within two working days;iii. A 60–90 min group video chat is organized every Sunday evening, following an interactive process of “sharing—Q&A—summary”;vi. Peer educators focus on experience sharing, presenting emotional management case studies every Tuesday and Thursday, and conducting monthly thematic sessions (e.g., “Postpartum Sleep and Emotional Regulation”), fostering a supportive atmosphere through positive reinforcement to encourage subject participation and mutual assistance.(5) Safety protocol: Intervention is terminated immediately if participants exhibit suicidal tendencies or harmful behaviors, with referral to psychiatric care.

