### Sample size

2.9

The sample size has been calculated according to the results from a previous clinical trial (27). The primary outcome in present study is the response rate at the end of 6-week intervention. Referring to the study of Uebelacker et al. (27), the response rate of health education group is 28.3% (responders). This study assumed that the effective rate of IPE combined with RHE was 70%. A two-sided test is required (25), *α* = 0.05, the sample size ratio of the two groups N1: N2 = 1:1 (i.e., the number of cases in the two groups is equal), *β* = 0.2, and the power of the test is 1-*β* = 80%. The analysis result is N1 = N2 = 38 cases, and 44 cases are included in each group according to the dropout rate of 15%. Therefore, a total of 44 patients/group ×2 groups = 88 patients will be included in this study.

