### Statistical analysis plan

2.10

The statistical analysis will be conducted by independent statisticians who will be blinded to group allocation and intervention methods. Before data analysis, the research group will draw up a statistical plan, including the required data and method of data processing. For Categorical data, we performed the Chi-square (x^2^) test for between-group differences. For continuous and normally distributed data, we performed Student’s *t*-test for between-group differences and paired t test for within-group differences. If data were distributed nonnormally, the Mann–Whitney U test for between-group differences and the Wilcoxon test for within-group differences would be used. The normally distributed data were expressed as the mean ± standard deviation. Nonnormally distributed data would be expressed as the median or interquartile range (IQR). For categorical variables, the X^2^ test will be used to examine the between-group differences, and percentages and frequencies will be presented to describe the effect size.

For longitudinal data analysis considering the repeated measurements at assessment nodes in this study, the Generalized Estimating Equations (GEE) model will be employed.

Fixed effects structure: It will include the group variable (experimental vs. control), time points (six assessment nodes as a categorical variable), and the interaction term between group and time points. Additionally, potential confounding variables (e.g., baseline characteristics that show imbalance between groups) will be incorporated into the model as covariates to adjust for their effects.

Correlation structure: Given the repeated measurements within individuals over time, the exchangeable (compound symmetry) correlation structure will be initially assumed, which posits that the correlation between any two measurements from the same individual is equal. Sensitivity analyses will be conducted using other correlation structures (e.g., autoregressive of order one, which assumes a higher correlation between measurements that are closer in time) to assess the robustness of the results. The working correlation matrix will be estimated based on the observed data during model fitting.

All clinical data analyses will be performed using SPSS V.22.0 software. Missing data will be handled using the multiple imputation method. A two-tailed test will be conducted, and a *p* < 0.05 will be considered statistically significant.

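### IPE is delivered in shared WeChat groups, but the listed tests treat IPE patients as independent; if outcomes are correlated within group, the test of no average effect is too liberal

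*Protocol article*

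**What the plan says.** Section 2.6.1.2 (Procedures) makes the group the vehicle of treatment: "Enrolled subjects are assigned to WeChat education groups (maximum 11 subjects per group) containing steering group members, peer educators, and participants". Within it, "A 60–90 min group video chat is organized every Sunday evening", peer educators present cases twice a week, and members are encouraged to help one another. Educators report weekly on the group, and the guidance team adjusts in response.

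Section 2.6.5 delivers RHE by telephone and outpatient interview and describes no groups. Both arms receive RHE, so the grouping is an added feature of the IPE arm alone.

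Section 2.10 names the chi-square test for categorical data, Student's t or Mann–Whitney U for continuous data, and a GEE for the repeated measurements. On correlation it says: "Given the repeated measurements within individuals over time, the exchangeable (compound symmetry) correlation structure will be initially assumed". The alternative structure offered for sensitivity, autoregressive of order one, also works within the person. The sample size in section 2.9 has no design effect. WeChat group and peer educator appear in neither section.

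**The concern.** Patients are randomised individually, but those in the IPE arm are then treated together. A group that works well or badly can move its members' outcomes in the same direction through the weekly chats, mutual support and locally adjusted content. Section 2.6.3.3 itself foresees a shared negative dynamic, with members made anxious by comparing parenting experiences.

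Where this happens, 44 IPE patients carry less information than 44 independent patients. The listed tests cannot see the loss, because group membership enters none of them. The p-value for the treatment comparison would be too small, as would the width of any interval derived from the same models. This is an issue with the analysis as stated, since section 2.10 specifies the tests, the GEE terms and the correlation structures.

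**Working it through.** **Inputs from the protocol article.** 44 per arm (section 2.4); 38 per arm before dropout, 28.3% versus 70% response, two-sided 5% (section 2.9); at most 11 per WeChat group (section 2.6.1.2). Hence at least 44/11 = 4 groups.

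**Assumptions.** The ICC is not given; 0.02, 0.05 and 0.10 are used. The design effect in the RHE arm is taken as 1.

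**The plan's own figure.** The pooled formula gives n = [1.96·√(2·0.4915·0.5085) + 0.842·√(0.283·0.717 + 0.70·0.30)]² / 0.417² = 22 per arm, or 26 with continuity correction. Neither is 38. That is a separate matter; 38 and 44 are used below as the planned sizes.

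**Level of the nominal 5% test.** For groups of size m:
- design effect in the IPE arm: DE = 1 + (m − 1)·ICC
- variance of the difference relative to the planned analysis: V = (1 + DE)/2
- actual level: 2·[1 − Φ(1.96/√V)]

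| m | ICC | DE | V | √V | Level |
|---|---|---|---|---|---|
| 11 | 0.02 | 1.20 | 1.10 | 1.049 | 6.2% |
| 11 | 0.05 | 1.50 | 1.25 | 1.118 | 8.0% |
| 11 | 0.10 | 2.00 | 1.50 | 1.225 | 11.0% |
| 3 | 0.02 | 1.04 | 1.02 | 1.010 | 5.2% |
| 3 | 0.05 | 1.10 | 1.05 | 1.025 | 5.6% |
| 3 | 0.10 | 1.20 | 1.10 | 1.049 | 6.2% |

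The m = 3 rows reflect slow entry. July 2023 to March 2025 is about 87 weeks. If recruitment is even (an assumption), 44/87 ≈ 0.5 IPE patients enter per week, so about 6 × 0.5 = 3 are in their six-week intervention at once.

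**Simulation check.** This used a beta-binomial model, Pearson chi-square, 44 per arm and four groups of 11. At a 28.3% response rate in both arms the level is 6.5%, 8.4% and 11.6% for the three ICCs (5.3% at ICC 0). At 50% it is 5.6%, 7.4% and 10.6% (4.5% at ICC 0). The formula is confirmed to within what the discreteness of the test allows.

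**Power at 28.3% versus 70%, ICC 0.05, 38 per arm.**
- Four groups averaging 38/4 = 9.5: DE = 1 + 8.5·0.05 = 1.425. Null SE = √(0.4915·0.5085·2.425/38) = 0.1263; alternative SE = √[(0.2029 + 0.21·1.425)/38] = 0.1150. Power = Φ[(0.417 − 1.96·0.1263)/0.1150] = 93.0%.
- Unpooled SE with DE = 1.5: 0.417/√[(0.2029 + 0.21·1.5)/38] = 3.57; Φ(3.57 − 1.96) = 94.6%.

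Without clustering the pooled form gives 96.7%. All these figures use normal critical values and are optimistic when there are few groups.

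**The case against.** A reader might infer that the false-positive rate exceeds 5% as a matter of fact. The documents do not support that, for four reasons.

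- No ICC is given. At a very small one the excess can vanish: the simulation at ICC 0.01, 50% response and 44 per arm gives 4.9%.
- The inflation belongs to a null of zero average effect with groups that differ. Because patients are individually randomised, an IPE that affected nobody would induce no group correlation, and the test would keep its level.
- Eleven is a maximum size. With slow recruitment, and with the baseline visit only 0 to 7 days before the start (Table 1), fewer patients may share a group at any time. Shared educators over time could push the effective size back up.
- It is tempting to say that each group has its own educators, so that one poor educator affects a quarter of the arm. The article does not say that educators differ between groups. Centrally curated content, double content review (section 2.6.4.1) and the 80-point competency threshold (section 2.6.2) would all reduce differences between groups.

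Two smaller points also stand. Section 2.10 specifies p-values and no confidence intervals, so narrow intervals are a concern only for intervals drawn from these models. It also promises a further statistical plan, which is not shown, so only the tests listed in the article can be judged.

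These points limit the size of the concern but do not remove it. Shared chats and mutual help can correlate outcomes even if educators overlap, and none of the listed tests would allow for that.

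**Conclusion.** The concern holds in conditional form. The listed tests ignore a grouping that the intervention creates in one arm. If within-group correlation is positive, the standard error is too small and the test of no average effect is too liberal. For assumed ICCs of 0.02 to 0.10 the level is about 6% to 11% with four groups of 11, and about 5.2% to 6.2% if effective group size is about 3. The result rests on the assumed ICC, on the group sizes, and on RHE having no comparable clustering. Power at the assumed effect is not the problem; the risk lies in the p-value and the stated precision, and it matters most if the observed effect is well below the assumed one.

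**What to change.** Record each IPE patient's WeChat group and the peer educators who served it. In the statistical plan promised in section 2.10, prespecify an analysis that allows for clustering in the IPE arm only, by one of two routes:

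- a partially nested model, with a random intercept for WeChat group in the IPE arm, each RHE patient as her own cluster, and small-sample degrees of freedom; or
- a comparison adjusted by the design effect over a stated ICC range. With four groups of 11 the critical value becomes 1.96·√V, that is 2.06, 2.19 and 2.40 at ICC 0.02, 0.05 and 0.10.

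The second route deserves a place because, with perhaps only four groups and a binary outcome, a random-intercept variance is poorly estimated. An ordinary GEE clustered on so few groups would be unreliable as well. Report the clustered result beside the independent-patient analysis with the estimated ICC, and claim an effect only if the conclusion holds with clustering allowed for.

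The cost is one or two recorded variables and some model wording; treatment and recruitment do not change. The downside is wider intervals and an imprecise ICC. Even an imprecise ICC is useful, since the article's conclusion says the trial should supply data for powering a larger one.
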